**Table 2 Tab2:** **Schedule for observation, testing, and assessment**

**Acquisition means**	**Examination items**	**Timing (allowable range)**		
		Baseline: week 8 before enrollment through day of enrollment	Week 12 (±4 weeks)	Day of study discontinuation or day of study completion at week 24 (±4 weeks)
Case report form	Patient background	×		
	Combined therapy	×	×	×
	Symptoms (NYHA class and self-assessment of daytime sleepiness)	×	×	×
	Quality of life and activities of daily living	×	×	×
	Vital signs	×	×	×
	Physical examination	×	×	×
	Echocardiography	×	×	×
	Chest X-ray	×	×	×
	Brain natriuretic peptide	×	×	×
	Hematology	×	×	×
	Sleep study	×^1^	×	Wherever possible^2^
	Cardiac event		×	×
	Usage of the ventilator in the ASV group	×	×	×
	Adverse events		×	×
Electronic means	Echocardiogram	×	×	×
	Air flow in the sleep study	×^1^		Wherever possible^2^
	Usage of the ventilator in the ASV group		×	×

^1^Without the ASV device, a device for sleep study (type 1, 2, or 3) is used. ^2^Without the ASV device, a device for sleep study (types 1, 2, 3, or 4) is used. ASV, adaptive servo-ventilation; NYHA, New York Heart Association.

### Statistical methods and sample size

The subgroup analysis of patients with reduced LVEF (<40%) in SAVIOR-R revealed a 6.9% improvement (before ASV therapy: 26.5 ± 7.4%; after ASV therapy: 33.4 ± 13.0%). In SAVIOR-R, furthermore, a statistical analysis considering time-course changes in LVEF indicated that the LVEF-improving effect of ASV therapy tended to appear at week 12 of the study or later. LVEF remained unchanged when ASV therapy was not conducted and improved by 5% when ASV therapy was conducted for 24 weeks. The target number of patients in SAVIOR-C was calculated based on an assumed standard deviation of 7.4 in reference to the pre-ASV therapy value. Consequently, power exceeds 80% when a group includes not less than 90 patients. Since sufficient power is obtained when a group includes 100 patients in consideration of a presumed withdrawal rate of 10%, a total of 200 patients—100 patients per study group—were established.

The efficacy analysis set consists of the full analysis set and the per-protocol set to be defined below. The full analysis set consists of patients who initiated ASV therapy, from whom the following patients are excluded: 1) patients in the ASV group who never used the ventilator during the study period; and 2) patients from whom the efficacy data after study onset were not obtained at all during the study period. The per-protocol set consists of patients in the full analysis set, from whom the following patients are excluded: 1) patients who deviated from the inclusion criteria or fell under any of the exclusion criteria; 2) patients who fell under any of prohibited combination therapies; and 3) patients with poor compliance in ventilator use. Poor compliance is defined as an ASV therapy practice rate of < 80% (number of days from day of treatment onset through day of treatment discontinuation or day of study completion). The safety of the study groups will be analyzed statistically on an intention-to-treat basis.

The aim of the statistical analyses is to examine the efficacy and safety of ASV therapy for the target number of 200 patients by comparing the ASV group with the control group with respect to the primary endpoint for efficacy—LVEF—and to the measured values of respective secondary endpoints. The detailed procedures for randomized assignment will be determined but will not be informed to the subinvestigators at each participating medical institution. The details and technical methods of the statistical analyses will be described in the statistical analysis plan to be prepared prior to database lock. Statistical tests (for example, chi-square test using the contingency table, Fisher’s exact probability test, Kruskal-Wallis test, and analysis of variance) will be used in accordance with the scale of demographic data. Furthermore, a two-tailed probability of 15% will be established as an index of intergroup homogeneity. The data to be collected in the present study will be analyzed by the Japan-Clinical Research Support Unit that is completely independent from study organizations.

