## Methods/Design

### Study design and study organization

The present study (SAVIOR-C) is a confirmatory, prospective, multicenter, collaborative, open-label, blinded-endpoint, parallel-group, randomized, controlled study. The target number of patients is 200, and the study groups consist of the ASV group and the control group. The present study will last for 24 weeks, and the primary and secondary endpoints will be assessed at baseline (8 weeks prior to treatment onset through treatment onset), at week 12 of study (±4 weeks), on the day of study discontinuation, or on the day of study completion at week 24 (±4 weeks).

The Steering Committee will perform activities (for example, selection of study sites, investigators, and others, preparation and revision of the protocol and other documents, interpretation of questions about the study plan, coordination with investigators, establishment of the handling criteria for patients and data, determination of the acceptance of patients and data, interpretation of the study results, and preparation of study conclusions; Additional file 1). The Central Adjudication Committee will confirm in a blind manner the absence of any problems in measurement conditions and results of two-dimensional echocardiographic parameters, including LVEF—the primary endpoint—and in the subinvestigator’s assessment on CHF deterioration—the secondary endpoint, and will check whether adverse events and ventilator failure have developed in a biased fashion to a given group. The Study Promotion Committee will afford study support to study sites. The present study has been approved by the Ethical Review Board at each participating medical institution (Additional file 2) before its conduct in accordance with the Declaration of Helsinki. Prior to enrollment, all patients will provide written informed consent to be involved in the present study. The present trial is registered (UMIN identifier: UMIN000006549, registered on 17 October, 2011).

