### Study treatment

Study treatment initiates within 8 weeks after provision of the verbal and written explanations by the investigator to each patient. Eligibility check, enrollment, and randomization of each patient are performed between the provision and the study onset. Patients in the ASV group undergo ASV therapy in addition to guideline-directed medical therapy [11] for the study period (study onset through week 24 of study), while patients in the control group undergo only guideline-directed medical therapy for the study period. Patients in the ASV therapy group, who are in bed, undergo the ASV therapy each night during the study period.

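### No efficacy analysis set is as-randomised: the full analysis set is worded around starting ASV and drops never-users from the ASV arm only

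*Protocol article*

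**What the plan says.** All the set definitions stand in the protocol article, section Statistical methods and sample size.

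- Two sets serve efficacy: "The efficacy analysis set consists of the full analysis set and the per-protocol set to be defined below".
- Base of the full analysis set: "The full analysis set consists of patients who initiated ASV therapy, from whom the following patients are excluded".
- Exclusion 1: "patients in the ASV group who never used the ventilator during the study period".
- Exclusion 2: "patients from whom the efficacy data after study onset were not obtained at all during the study period".
- The per-protocol set starts from the full analysis set and removes further patients, among them "patients with poor compliance in ventilator use", defined as an ASV practice rate below 80%.
- For safety the rule is different: "The safety of the study groups will be analyzed statistically on an intention-to-treat basis".

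The section Study treatment says of the other arm that "patients in the control group undergo only guideline-directed medical therapy for the study period". The Abstract states a superiority objective, and the closing part of Statistical methods and sample size says that the two groups are compared on LVEF and the secondary endpoints. The article does not say which of the two efficacy sets is primary.

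**The concern.** There are two faults, one of wording and one of substance.

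The wording ties membership of the full analysis set to starting a treatment that controls never receive. The set as written cannot support the comparison that the same section calls for.

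The substantive fault remains once the wording is repaired. Whether a patient ever used the ventilator is known only after randomisation and only in the ASV arm. Control patients who would not have started ASV had they been assigned to it cannot be identified, so they stay in. The retained ASV patients are then compared with an unselected control group, and randomisation no longer guarantees that the two are alike. Blinded review of the echocardiograms does not help, because the selection lies in who is analysed and not in how LVEF is read.

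What is at stake is the validity of the test that the trial describes as confirmatory. Clinical events are affected too. They are a secondary efficacy endpoint, and a death or hospitalisation in a never-user would fall outside both efficacy sets.

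**Working it through.** **Step 1. Who is in each efficacy set**

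| Patient | Full analysis set, literal | Full analysis set, read as started study treatment | Per-protocol set |
|---|---|---|---|
| Control with post-onset data | out | in | in, unless ineligible or on a prohibited therapy |
| ASV, used the device, has post-onset data | in | in | in only if practice rate is at least 80%, and subject to the same two conditions |
| ASV, never used the device, has post-onset data | out | out | out |
| Either arm, no post-onset data | out | out | out |

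The per-protocol column uses the charitable reading. Under either reading the third row is removed from both efficacy sets, and it has no counterpart among controls. The per-protocol set cannot restore these patients because it is a subset. So the conclusion does not depend on which set is primary.

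**Step 2. The plan's own figures**

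Inputs from Statistical methods and sample size: difference 5 LVEF points, SD 7.4, 90 per group, 10% withdrawal. The significance level is not stated, so two-sided 5% is assumed here and below (normal approximation).

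- SE = 7.4 × √(2/90) = 1.103.
- Power = Φ(5/1.103 − 1.96) = Φ(2.57) = 99.5%. The claim that power exceeds 80% is true, although these inputs reach 80% with 35 per group. That is a separate matter, and nothing here rests on it.
- 90/(1 − 0.10) = 100 per group, as stated.

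**Step 3. What dropping never-users can do**

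Let f be the share of ASV patients who never use the device, and g the shortfall in their mean LVEF change relative to users. If u is the mean in users, the mean of the whole ASV arm is (1 − f)u + f(u − g) = u − fg. Analysing users alone therefore shifts the ASV mean by +fg relative to the as-randomised arm. The documents give neither f nor g. Both are assumptions.

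Take no true effect, 100 controls, 100(1 − f) ASV users and SD 7.4:

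- SE = 7.4 × √(1/100 + 1/(100(1 − f)))
- Type I error = 1 − Φ(1.96 − fg/SE) + Φ(−1.96 − fg/SE)

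| f | g (points) | Bias fg | SE | Type I error |
|---|---|---|---|---|
| 2% | 5 | 0.10 | 1.052 | 5.1% |
| 5% | 5 | 0.25 | 1.060 | 5.6% |
| 10% | 5 | 0.50 | 1.075 | 7.5% |

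If never-users do better than users, g is negative and the bias runs against ASV by the same amount.

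**Step 4. What keeping them costs**

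Suppose the effect is 5 points in users and 0 in never-users. With f = 10% the as-randomised difference is 5 × 0.90 = 4.5. At 90 per group, power = Φ(4.5/1.103 − 1.96) = Φ(2.12) = 98.3%.

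**The case against.** Several objections have force.

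- *The missing control group is a slip.* A reader might infer that the trial plans to analyse ASV patients only. The documents do not support that. Exclusion 1 names patients in the ASV group, which implies that others belong to the set, and it would be redundant if the base already required ASV to have been started. The group comparison is stated in the same section. This stands: the wording needs correcting but is not a design decision.
- *The illustration may be too severe.* A 10% share of never-users equals the plan's whole withdrawal allowance, inclusion criterion 4 in Table 1 requires patients capable of using the device at home, and a 5-point shortfall equals the whole target effect. Some never-users would also have no follow-up echocardiogram and be lost under exclusion 2 anyway. Non-starters could be the less symptomatic patients, which would reverse the direction. All this stands, and the figures show scale only.
- *The analysis plan may settle it.* This does not stand. The article leaves technical detail to that plan but states the set definitions itself, and a plan that follows them inherits the fault.

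Three further inferences are tempting and should not be drawn.

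- The 8 weeks in Study treatment are not a delay between randomisation and treatment. They run from the explanation given to the patient, and randomisation falls inside that window.
- Patients who try ASV, cannot tolerate it and stop are not removed by exclusion 1. It reaches only those who never used the device.
- The final assessment is made "on the day of study discontinuation, or on the day of study completion at week 24", but the article does not say that an early value replaces the week-24 value, or that stopping ASV ends follow-up.

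**Conclusion.** The point holds as a fault in the stated definitions. The base wording contradicts Study treatment and the planned group comparison. On any reading, both efficacy sets remove randomised patients through a post-randomisation criterion that can act in one arm only, and intention-to-treat is reserved for safety. For a confirmatory, open-label superiority trial this must be changed.

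Confidence is high for the definition and low for the consequence. The share and prognosis of never-users are not given, so the bias may be nil, may favour ASV or may favour control. Under the assumptions of the illustration (never-users 5 points worse, SD 7.4, two-sided 5%), the type I error goes from 5% to about 5.6% at a 5% share and about 7.5% at a 10% share, with negligible inflation at 2%. The reason for the change is that a confirmatory test should not depend on a share that nobody knows in advance.

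**What to change.** Before database lock, amend the definitions in Statistical methods and sample size and carry them into the analysis plan:

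1. Define the full analysis set as all randomised patients, analysed in their assigned group whether or not ASV was started.
2. Delete exclusion 1.
3. Keep the absence of any post-onset efficacy data only as a data-availability limit for the LVEF analysis.
4. Count clinical events in all randomised patients.
5. Name this set as primary, and keep the present set, with its base wording corrected to include controls, as a sensitivity analysis.

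The change is one of wording. Its downside is that the effect estimate may be slightly smaller, because never-users dilute it: 4.5 in place of 5 points in the 10% example, with power of 98.3% on the plan's inputs. That small cost relies on the planned SD of 7.4. At 13.0, the SD that the article reports after ASV in the earlier observational study, power at 90 per group would be 73.2% for 5 points and 64.1% for 4.5.

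### The per-protocol compliance rate is counted only up to treatment discontinuation, with no minimum exposure, so ASV patients who stop very early can be kept as compliant

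*Protocol article*

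**What the plan says.** All of this is in the protocol article. Under Statistical methods and sample size, the efficacy sets are a full analysis set and a per-protocol set drawn from it. The per-protocol set leaves out "patients with poor compliance in ventilator use", and the article adds: "Poor compliance is defined as an ASV therapy practice rate of < 80" per cent. The only explanation of the rate is a parenthesis giving one day count: "number of days from day of treatment onset through day of treatment discontinuation or day of study completion". Numerator and denominator are not labelled, and no minimum duration of use is given.

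Two full-analysis-set exclusions decide who can reach the per-protocol set: "patients in the ASV group who never used the ventilator during the study period" and "patients from whom the efficacy data after study onset were not obtained at all during the study period".

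Under Study treatment, ASV patients are to "undergo the ASV therapy each night during the study period", which lasts 24 weeks, while "patients in the control group undergo only guideline-directed medical therapy for the study period". Table 2 schedules echocardiography at baseline, at week 12 and at a final visit headed "Day of study discontinuation or day of study completion at week 24 (±4 weeks").

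The sample-size text says that in the earlier observational study the LVEF effect tended to appear from week 12 onwards. It works with a 5-point gain after 24 weeks of ASV.

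**The concern.** A per-protocol set is meant to show the effect in patients who received the treatment roughly as planned. If the compliance clock stops when the patient stops, the rate measures how regularly the device was used while it was used, not how much of the planned course was received. Someone who gives up after two weeks may then count as a complier. Because the plan expects benefit only from about week 12, such a patient would not be expected to show it, and the per-protocol contrast would be pulled towards zero.

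A second matter affects how the result is read. Controls have no ventilator, so this exclusion can remove ASV patients only. The ASV arm is conditioned on adherence and the control arm is not. Adherence may go with prognosis, so the contrast is no longer protected by randomisation.

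**Working it through.** The article gives no derived figure for the compliance rule, so there is none to reproduce.

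**Inputs from the article.** Threshold 80%; ASV every night for 24 weeks, so 24 × 7 = 168 planned nights; completion at week 24 ± 4 weeks, so 140 to 196 nights; target effect 5 LVEF points; SD 7.4; effect expected at week 12 (84 nights) or later.

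**Step 1: the rule on its natural reading.** Rate = nights used ÷ nights from onset to discontinuation or completion, compared with nights used ÷ 168.

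| Pattern of use | Rate as written | Share of 168 nights |
|---|---|---|
| 7 of 7 nights, then stops | 7/7 = 100% (kept) | 7/168 = 4.2% |
| 12 of 14 nights, then stops | 12/14 = 85.7% (kept) | 12/168 = 7.1% |
| 28 of 28 nights, then stops | 28/28 = 100% (kept) | 28/168 = 16.7% |
| 84 of 84 nights, then stops | 84/84 = 100% (kept) | 84/168 = 50.0% |
| 130 of 168 nights, completes | 130/168 = 77.4% (excluded) | 77.4% |

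The first three patients stop well before week 12. The last row is the same in both columns (the cut is 0.8 × 168 = 134.4 nights), so the choice of denominator does not affect that patient.

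**Step 2: can such a patient reach the set?** Yes. One night of use avoids the never-used exclusion. One efficacy value after onset avoids the no-data exclusion, and Table 2 provides an echocardiogram at study discontinuation. A patient who stops ASV but stays in the study has the later scheduled visits as well.

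**Step 3: the other reading of the parenthesis.** If the day count were the numerator over planned days, the patient stopping on day 14 would score 14/168 = 8.3% and be excluded. But anyone completing at week 24 would score 168/168 = 100% whatever the nightly use, and the rule would not measure compliance. That reading is unlikely.

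**Step 4: dilution (shares assumed).** If a share q of the ASV patients in the set are early stoppers with no effect, the expected difference is 5 × (1 − q): 4.75 points for q = 5%, 4.5 for 10%, 4.0 for 20%.

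**Step 5: one-armed selection (all assumed).** Suppose a share p of ASV patients is excluded, adherence correlates r with LVEF change, and the SD of change is 7.4. The shift in the ASV mean with no true effect is r × 7.4 × φ(z_p)/(1 − p), where φ is the standard normal density and z_p its p-quantile.

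- p = 0.1, r = 0.1: 0.1 × 7.4 × 0.1755/0.9 = 0.14 points
- p = 0.2, r = 0.2: 0.2 × 7.4 × 0.2800/0.8 = 0.52 points
- p = 0.3, r = 0.3: 0.3 × 7.4 × 0.3477/0.7 = 1.10 points

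Under these assumptions the shift favours ASV, while step 4 works against it. The article gives neither p, q nor r.

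**The case against.** The strongest reply is that the parenthesis is a fragment in a condensed article. The full protocol or the SAP, which is still to be prepared before database lock, may state the formula. That limits certainty about the reading. But the article does set out to define the sets, and the alternative reading in step 3 is also defective, so the wording needs correcting either way.

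Several stronger claims are tempting, and the document does not support them.

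- A reader might infer that the clock wrongly drops long-term users. It does not: the patient with 130 of 168 nights fails under either denominator. That is an objection to having an 80% threshold.
- A reader might infer that untreated patients enter the set. Never-users are already removed from the full analysis set; barely exposed is the most that can be said.
- A reader might treat the one-armed exclusion as an error peculiar to this plan, against a wholly unselected control arm. Any device-compliance criterion is one-sided when controls have no device, and the exclusions for eligibility and prohibited therapy apply to both arms. It is a limit to acknowledge.
- A reader might infer that the efficacy claim is to rest on the per-protocol set. The article does not say so. It does not rank the two sets, and that ranking may properly be left to the SAP.

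**Conclusion.** The point holds in a limited form. As worded, and on its natural reading, the rule can keep ASV patients with a few per cent of planned exposure (7% in the 12-of-14 example), although the plan itself expects benefit only from about week 12. This is a misclassification built into a stated definition.

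Its effect on the estimate depends on how many patients stop early, which the article does not give. The 4.75-to-4.0-point range assumes 5% to 20% early stoppers with no benefit. It would be going too far to claim a known upward bias from conditioning one arm on adherence: the 0.14-to-1.10-point range rests wholly on assumed exclusion shares and correlations, and dilution opposes it. The size of the selection bias cannot be determined from the document, and the net direction is uncertain. That uncertainty is itself a reason not to use the per-protocol result as more than support.

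**What to change.** Write out the numerator and denominator of the practice rate.

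- **Patients who discontinue ASV:** nights used ÷ days from onset to scheduled week-24 completion, or to death if earlier, so that nights after stopping count as not used. The 12-of-14 patient then scores 7.1% and is excluded.
- **Completers:** nights used ÷ actual days to the completion visit. A flat 168 would fit the visit window badly: its cut of 135 nights would demand 135/140 = 96% from someone completing at week 20, and only 135/196 = 69% at week 28. Actual days keep the requirement at 80%: 112 of 140 nights, or 157 of 196.

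State also that the per-protocol analysis is supportive, because its compliance exclusion conditions only the ASV arm on adherence, and that the full analysis set carries the efficacy conclusion.

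The cost is a few lines of wording before database lock; ventilator use is already collected electronically in the ASV group. The per-protocol set will be smaller. Ending the count at death leaves a short denominator for early deaths, so the number of such patients in the set should be reported.
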